### 5.1.3 REASONS FOR SETTING

#### Criteria for inclusion

- 1) Set from an ethical point of view.
- 2) To select the appropriate age for evaluation of the study drug.
- 3) To select patients diagnosed with eligible diseases.

#### Criteria for exclusion

- 1) - 11) Set from the viewpoint of the efficacy of the study drug.
- 12) - 17) Set from the viewpoint of safety of subjects (mother and fetus).
- 18) To exclude patients who were not eligible for the study.

## 5.2 TARGET NUMBER OF CASES

### 5.2.1 TARGET NUMBER OF CASES

Target number of cases: 50 in the test group and 50 in the control group (total 100 cases)

### 5.2.2 REASONS FOR SETTING THE NUMBER OF CASES

In this study, since fetal and neonatal deaths were considered to be at higher risk of developing BPD and infant deaths up to 36 weeks PMA were also considered as one of events, infant deaths up to 36 weeks PMA (5%) were also taken into account to establish effect sizes for the two groups.

In a previous foreign study, the incidence of BPD36 was 26.4% (29/110, all children survived) when 110 pregnant women who developed pPROM at <28 weeks of gestation were treated with AZM. In a previous study in Japan, the incidence of BPD36 was 18.2% (2/11, all children survived) when 11 pregnant women with pPROM at <28 weeks of gestation were treated with ABPC/SBT + AZM. In addition, when ABPC/SBT + AZM was administered to 10 pregnant women with pPROM at <28 weeks of gestation from June 2013 to May 2020 at Saga Hospital, the incidence of BPD36 was 40.0% (4/10, all children survived) ([name] *et al*, unpublished data). Based on the above, the incidence of moderate or severe BPD36 or child death by 36 weeks PMA in the intervention group (AZM group) was assumed to be 18.0% to 40.0%.

On the other hand, the literature search did not retrieve any reports of EM administration to pregnant women with pPROM at <28 weeks' gestation alone. Therefore, we assumed that the incidence rate of moderate or severe BPD36 or infant death by 36 weeks PMA in the control group (EM group) was 60.0% based on the general BPD36 incidence rate.

The median number of weeks of gestational duration for pregnant women with pPROM is 2 weeks. Based on the annual number of deliveries, the number of births by week, and the percentage of pPROM, we can estimate that 1,200 newborns per year are born at <30 weeks to pregnant women with pPROM complications. In the 20 regional and comprehensive perinatal centers scheduled to participate in this study, the number of cases is estimated to be approximately 200 per year over a 2-year period. Assuming that 50% of the patients meet the eligibility criteria for this study and consent is obtained, 100 patients can be enrolled over a two-year period, and from the viewpoint of feasibility, the target number of cases for this study was set at 100. Under a two-tailed test and a significance level of 5%, the power of detection ranged from 0.516 to 0.995 when the assumed BPD36 incidence rate in the intervention group was 18.0% to 40.0%, which is considered to guarantee a power of at least 0.5.

For reference, the power curve for the BPD36 incidence rates of 18.0% to 60.0% in the intervention group are shown below. In addition, the incidence rates in previous foreign and domestic studies and the study at Saga Hospital are indicated by red lines.

[figure not shown]

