Some infants with moderate/severe BPD36 show continued respiratory failure beyond the neonatal period, and they need long-term oxygen and/or respiratory support. After school age, central nervous system effects are also seen, including decreased brain capacity and lower IQ in cognitive and language development. Although much research and treatment has been done, the incidence is still high, around 50%, and has a significant impact on the prognosis of very low birth weight infants.

It has been reported that pPROM is an independent risk factor for BPD. We analyzed 55 pregnant women with singleton pregnancy who had pPROM at <28 weeks of gestation, and delivered between 22 and 31 weeks of gestation, and we investigated the association between pPROM and the subsequent occurrence of short- and long-term prognoses; perinatal death occurred in 13% (intrauterine death: 6%, early neonatal death: 7%), pulmonary hypoplasia in 14%, respiratory distress syndrome (RDS) in 56%, transient tachypnea of newborn (TTN) in 42%, NEC

in 6%, IVH in 10%, PVL in 10%, sepsis in 4%, BPD at 28 days of life (BPD28) in 72%, and BPD36 in 60% .

Since supportive care such as oxygen therapy is the only treatment for BPD, the prevention of BPD is strongly desired. To this end, it is very important for women with pPROM occurring at <28 weeks of gestation to receive appropriate antibiotics, and to prolong the pregnancy period.

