## 4.2 RANDOMIZATION

Allocation will be done by REDCap in the order of registration. REDCap will assign subjects (maternal and fetal) who meet all inclusion criteria to the intervention or control group 1:1 by stratified allocation. Because the incidence of BPD varies with the number of weeks of gestation at the onset of pPROM (22 weeks 0 days to 23 weeks 6 days and 24 weeks 0 days to 27 weeks 6 days) and facility (early caffeine-using facility or early caffeine-unused facility), stratification factors will be used at the time of randomization. The implementing facility will be surveyed prior to participation to determine if the facility is an early caffeine using facility.

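### Section 5.2.2 promises power of at least 0.5 on a margin of 1.6 points, using rates in which the stated 5% deaths cannot be seen and with no allowance for exclusions or missing outcomes

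*Protocol*

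**What the plan says.** Section 5.2.1 sets the target at "50 in the test group and 50 in the control group (total 100 cases", and section 4.2 randomises women "to the intervention or control group 1:1 by stratified allocation".

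Section 5.2.2 justifies the number in three steps.

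- **Event rates.** It states that "infant deaths up to 36 weeks PMA (5%) were also taken into account to establish effect sizes for the two groups", and labels the assumed rates as BPD36 of at least moderate severity or death by 36 weeks. For AZM it cites three series with BPD36 in 29/110, 2/11 and 4/10, each reported without deaths; the last is "40.0% (4/10, all children survived". It then assumes 18.0% to 40.0%. For EM it assumes 60.0%, which it attributes to the general BPD36 rate.
- **Feasibility.** Eligible cases at the 20 centres are put at "approximately 200 per year over a 2-year period". Half are expected to qualify and consent, giving 100 over two years.
- **Power.** "Under a two-tailed test and a significance level of 5"%, power runs from 0.516 to 0.995 over the AZM range, "which is considered to guarantee a power of at least 0.5". The rate entered is called a BPD36 incidence rate at this point, not a composite rate.

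Two rules elsewhere bear on the calculation. Section 14.1 removes from the full analysis set (FAS) randomised women who were never treated, have no post-treatment data or prove ineligible. Section 14.2.2 counts a missing primary outcome in that set as an event.

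**The concern.** The text says deaths are in the effect sizes, yet the ends of the AZM range match 2/11 (18.2%) and 4/10 (40.0%) with nothing visibly added. The power figure also leaves no room for the exclusions and the missing-as-event rule that the protocol fixes in section 14.

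The lower power figure is 0.516, so the claimed floor of 0.5 rests on 1.6 points. A shortfall that small would be trivial for a conditional estimate. It matters here because the section presents the floor as assured.

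At stake is what readers are told. The ethics committee and the funder see a minimum power that the design does not secure. Section 14.2.2 still specifies a two-sided test at 0.05, and section 2.2 makes the move to Phase III depend on the result. Separately, feasibility is the stated basis for choosing 100, and the sentence giving it does not add up.

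**Working it through.** **Inputs.** Two-sided alpha 0.05, 60% against 40% or 18%, and 5% deaths (section 5.2.2); n = 50 per arm (section 5.2.1). The protocol gives no exclusion or missing-data rates, so those below are assumptions shown as ranges.

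**Formula.** Pooled-variance z-test without continuity correction, with p̄ the mean of the two rates:

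power = Φ{ [ |p1 − p2| − 1.96·√(2p̄(1 − p̄)/n) ] / √( [p1(1 − p1) + p2(1 − p2)]/n ) }

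**Step 1: reproduce the plan's figures.**

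- 60% v 40%, n = 50: (0.20 − 1.96 × 0.1000)/0.0980 = 0.041, power 0.5163.
- 60% v 18%, n = 50: (0.42 − 1.96 × 0.0976)/0.0881 = 2.60, power 0.9953.

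Both match the stated 0.516 and 0.995. The calculation therefore uses 60%, 40% and 18% as they stand, with all 50 per arm analysed.

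**Step 2: put the stated 5% deaths in at the weak end.** If BPD36 rates apply to survivors, composite = 0.05 + 0.95 × BPD rate.

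| How deaths enter | EM v AZM | Power |
|---|---|---|
| 0.05 + 0.95p in both arms | 62% v 43% | 0.477 |
| Flat 5 points in both arms | 65% v 45% | 0.520 |
| 60% already includes deaths; AZM raised by 0.05 + 0.95p | 60% v 43% | 0.396 |
| 60% already includes deaths; AZM raised by 5 points | 60% v 45% | 0.322 |

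**Step 3: exclusions alone (assumed), 60% v 40%.** 48 per arm 0.4998; 47 per arm 0.491; 45 per arm 0.475.

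**Step 4: missing outcomes counted as events alone (assumed fraction m), n = 50.** Each rate becomes m + (1 − m)p. m = 2%: 0.500; 3%: 0.492; 5%: 0.477; 10%: 0.439.

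**Step 5: 5% deaths plus 5% missing as events.** AZM 0.05 + 0.95 × 0.43 = 45.85%; EM 0.05 + 0.95 × 0.62 = 63.9%; power 0.441.

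**Step 6: exact power of the same uncorrected test, by enumeration.**

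| Scenario | n per arm | Exact power |
|---|---|---|
| 60% v 40% | 50 | 0.543 |
| 62% v 43% | 50 | 0.503 |
| 60% v 40% | 48 | 0.511 |
| 60% v 40% | 47 | 0.495 |
| 62% v 43% | 48 | 0.471 |

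**Step 7: precision.** The 95% CI half-width at 60% v 40% is 1.96 × 0.0980 = 0.192, about 19 points.

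**Step 8: the other end.** At AZM 18% with 5% deaths as 0.05 + 0.95p (62% v 22.1%), power is 0.989. Only the 40% end is affected.

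**Step 9: recruitment.** 200 per year × 2 years × 0.5 = 200. The stated 100 needs 200 in total × 0.5.

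**The case against.** The best defence is that the power arithmetic is right and the claim is conditional on an AZM rate between 18% and 40%. The section also offers a power curve up to 60%, so lower power outside that range is disclosed. No deaths occurred in the AZM series, so there BPD36 and BPD36-or-infant-death coincide, and adding deaths is a planning judgement. A flat 5 points in both arms gives 0.520. Exact power of the uncorrected test is 0.543, and still 0.503 with 5% deaths. Section 7.7 allows women who have already consented to be enrolled beyond 100. Finally, this is an exploratory trial sized by feasibility; power near 0.5 already signals that a null result says little, and Phase III will be sized on observed rates.

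Much of this stands. Nothing here calls for more patients, and deaths alone need not break 0.5. It does not rescue a guarantee: the section never shows where its 5% enters, and the exact figure also falls below 0.5 with 47 per arm, or with 5% deaths and 48 per arm.

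A reader might infer three stronger claims that the documents do not support.

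- **That the control rate should be 50%.** The figure of about 50% in section 2.1.1 concerns very low birth weight infants generally. The same section reports BPD36 of 60% after pPROM before 28 weeks, and 76% to 41% at 22 to 27 weeks, so 60% is defensible.
- **That power is about 0.42, because "perinatal death occurred in 13% (intrauterine death: 6%, early neonatal death: 7"%.** Adding 13% deaths assumes that the 60% BPD36 in that cohort excludes them; no denominator is given.
- **That Fisher's exact test sets the figure, at 0.462.** The protocol names only a test of the difference in proportions.

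**Conclusion.** The point holds in a limited form. The range 0.516 to 0.995 is correct for 60% against 40% and 18% with 50 analysed per arm, so this is not a calculation error. What fails is the assurance of at least 0.5, together with the mismatch between the text, which says deaths are included, and the inputs, where they are not visible.

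Under the protocol's own type of calculation, the weak end lies at about 0.44 to 0.52, depending on how deaths, exclusions and missing outcomes enter. It would be 0.32 to 0.40 if the EM rate already contains deaths and only the AZM rate needs raising. That the 60% contains none is inferred from its attribution to a BPD36 rate; the protocol does not say so outright. The exclusion and missing-data rates are assumptions, but two exclusions per arm are enough to remove the margin on the pooled calculation.

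The recruitment sentence contradicts itself whatever view is taken of power. It does not affect the power figures.

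**What to change.** Keep 100 women and amend section 5.2.2 as follows.

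1. State the assumed composite rate for each arm and how the 5% deaths enter it, and say whether the EM 60% includes deaths.
2. Name the test behind the power figure.
3. State the assumed rates of exclusion from the FAS and of missing outcomes counted as events.
4. Replace the guarantee with a conditional range at the 40% end, about 0.44 to 0.52 under the assumptions above, and add the expected 95% CI half-width of about 19 points. If the EM 60% proves to include deaths, recompute the range.
5. Make the case count, the 50% and the 100 agree; for example, about 200 cases in total over two years, if that is what was meant.

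The cost is a text amendment and a less favourable stated power. Sample size, design and analysis do not change.

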## 6 INTERVENTION

### 6.1 DRUGS USED

#### 6.1.1 SUMMARY OF DRUGS

The following test and control drugs (study drugs) will be used in this study.

##### Test drug

|                                               |                                                                                                                                                                                                                                                                                                    |
|-----------------------------------------------|----------------------------------------------------------------------------------------------------------------------------------------------------------------------------------------------------------------------------------------------------------------------------------------------------|
| Generic name                                  | Sulbactam Sodium, Ampicillin Sodium for Injection                                                                                                                                                                                                                                                  |
| Product name/manufacturer                     | Sulbacillin 1.5g for Injection (Meiji Seika Pharma Co., Ltd.)                                                                                                                                                                                                                                      |
| Dosage form, product description, and content | Each vial contains 0.5 g (potency) of Japanese Pharmacopoeia Sulbactam Sodium and 1 g (potency) of Japanese Pharmacopoeia Ampicillin Sodium, and is an injectable solution to be dissolved during use.
White to yellowish-white powder, pH: 8.0-10.0 [1.5 g (potency)/10 mL, aqueous solution]. |
| Therapeutic category                          | Antibiotic preparations with beta-lactamase inhibitor                                                                                                                                                                                                                                              |
| Indications: susceptible strains              | Staphylococcus spp. (ABPC/SBT-sensitive), Streptococcus pneumoniae, Moraxella (branhamella) Catalysis, Escherichia coli, Proteus, Haemophilus influenzae                                                                                                                                           |
| Indications: adaptation disease               | Pneumonia, lung abscess, cystitis, peritonitis                                                                                                                                                                                                                                                     |
| Dosage and Administration                     | [Pneumonia, lung abscess, peritonitis] The usual adult dosage of sulbactam sodium ampicillin sodium is 6 g (potency) per day divided                                                                                                                                                               |

|                    |                                                                                                                                                                                                                                                                                                                                                                                                                                                  |
|--------------------|--------------------------------------------------------------------------------------------------------------------------------------------------------------------------------------------------------------------------------------------------------------------------------------------------------------------------------------------------------------------------------------------------------------------------------------------------|
|                    | 
into two doses for intravenous injection or intravenous drip infusion. In cases of severe infection, the dose may be increased as necessary, but should not exceed 3 g (potency) four times a day (12 g (potency) as the daily dose).
 
[For cystitis] Normally, for adults, sulfactam sodium ampicillin sodium is administered in two divided doses of 3 g (potency) per day by intravenous injection or intravenous drip infusion.
 |
| Storage conditions | Store at room temperature                                                                                                                                                                                                                                                                                                                                                                                                                        |

|                                               |                                                                                                                                                                                                                                                                                                                                                     |
|-----------------------------------------------|-----------------------------------------------------------------------------------------------------------------------------------------------------------------------------------------------------------------------------------------------------------------------------------------------------------------------------------------------------|
| Generic name                                  | Azithromycin Hydrate for Injection                                                                                                                                                                                                                                                                                                                  |
| Product name/manufacture                      | ZITHROMAC Intravenous use (Pfizer Inc.)                                                                                                                                                                                                                                                                                                             |
| Dosage form, product description, and content | Each vial contains 524.1 mg of Japanese Pharmacopoeia azithromycin hydrate (500.0 mg (potency) of azithromycin). White mass or powder (lyophilized), pH 6.2-6.8 (in solution at a concentration of 100 mg/mL dissolved in 4.8 mL of water for injection).                                                                                           |
| Therapeutic category                          | 15-membered ring macrolide antibiotic preparation                                                                                                                                                                                                                                                                                                   |
| Indications: susceptible strains              | Azithromycin-sensitive Staphylococcus spp., Streptococcus spp., Streptococcus pneumoniae , Neisseria gonorrhoeae , Moraxella (branchamella) catallis , Haemophilus influenzae , Legionella pneumophila , Peptostreptococcus , Prevotella , Chlamydia , Mycoplasma spp. |
| Indications: adaptation disease               | Pneumonia, lung abscess, cystitis, peritonitis                                                                                                                                                                                                                                                                                                      |
| Dosage and Administration                     | For adults, azithromycin is administered at a dose of 500 mg (potency) once daily over 2 hours by intravenous drip infusion.                                                                                                                                                                                                                        |
| Storage conditions                            | Store at room temperature                                                                                                                                                                                                                                                                                                                           |

|                                               |                                                                                                                                                                                                                                                                                                                                                     |
|-----------------------------------------------|-----------------------------------------------------------------------------------------------------------------------------------------------------------------------------------------------------------------------------------------------------------------------------------------------------------------------------------------------------|
| Generic name                                  | Azithromycin Hydrate Tablets                                                                                                                                                                                                                                                                                                                        |
| Product name/manufacture                      | ZITHROMAC tablets (Pfizer Inc.)                                                                                                                                                                                                                                                                                                                     |
| Dosage form, product description, and content | White film-coated tablets containing 262.0 mg of azithromycin hydrate (250 mg of azithromycin (potency) per tablet)                                                                                                                                                                                                                                 |
| Therapeutic category                          | 15-membered ring macrolide antibiotic preparation                                                                                                                                                                                                                                                                                                   |
| Indications: susceptible strains              | Azithromycin-sensitive Staphylococcus spp., Streptococcus spp., Streptococcus pneumoniae , Neisseria gonorrhoeae , Moraxella (branchamella) catallis , Haemophilus influenzae , Legionella pneumophila , Peptostreptococcus , Prevotella , Chlamydia , Mycoplasma spp. |
| Indications: adaptation disease               | Deep skin infection, lymphatic duct and lymphadenitis, pharyngolaryngitis, tonsillitis (including peritonsillar and peritonsillar abscess), acute bronchitis, pneumonia, lung abscess, secondary infection of chronic respiratory tract lesions, urethritis,                                                                                        |

|                           |                                                                                                                                                                                                                                                                                                                                                                                                                                                                                                                                                                                                                                                                                                                                                                                                           |
|---------------------------|-----------------------------------------------------------------------------------------------------------------------------------------------------------------------------------------------------------------------------------------------------------------------------------------------------------------------------------------------------------------------------------------------------------------------------------------------------------------------------------------------------------------------------------------------------------------------------------------------------------------------------------------------------------------------------------------------------------------------------------------------------------------------------------------------------------|
|                           | cervicitis, pelvic inflammatory disease, sinusitis, periodontitis, periapical inflammation, jaw inflammation                                                                                                                                                                                                                                                                                                                                                                                                                                                                                                                                                                                                                                                                                              |
| Dosage and Administration | 
<deep skin infections, lymphatic duct and lymphadenitis, pharyngolaryngitis, tonsillitis (including peritonsillar and peritonsillar abscess), acute bronchitis, pneumonia, lung abscess, secondary infection of chronic respiratory tract lesions, sinusitis, periodontitis, periapical inflammation, jaw infection>
 
For adults, azithromycin is administered orally at a dose of 500 mg (potency) once daily for a total of 1.5 g (potency) for 3 days.
 
<urethritis, cervicitis>
 
For adults, azithromycin is administered orally at a dose of 1000 mg (potency).
 
<pelvic inflammatory disease>
 
For adults, after treatment with azithromycin injection, azithromycin should be administered orally at a dose of 250 mg (potency) once daily.
 |
| Storage conditions        | preservation at room temperature                                                                                                                                                                                                                                                                                                                                                                                                                                                                                                                                                                                                                                                                                                                                                                          |

